#### Cases

Men aged 21–49 years.Men with a female partner aged 21–39 years.Couples who are not able to conceive for at least 12 months of regular, unprotected intercourse.Couples who are Singapore citizens or permanent residents.

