#### Controls

Men aged 21–49 years.Men with a female partner aged 21–39 years.Men with proven fertility indicated by female partners who are currently pregnant and with viable intrauterine pregnancy at gestational weeks of less than or equal to 16 at the time of the study.Couples with attempted time to conceive within 12 months to achieve this pregnancy.Couples who are Singapore citizens or permanent residents.

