### Data collection and management

During the study visit (the only single timepoint visit), trained research staff will collect data on the sociodemographics and medical history of participants through interviews and medical record collection forms. They will also gather self-reported data on behavioural, lifestyle and environmental factor exposures from the past month using standardised questionnaires. The selection of the recall timeframe is based on the period specified in the validated questionnaires (table 1). Additionally, the staff will conduct anthropometric and body fat composition measurements, and collect blood, urine and semen samples from participants at the clinics in KKH. All data will be saved in a REDCap database. Access to this database is secured with a password, and only approved study team members can access the stored information.

**Table 1 T1:** Data and biosamples collected from both case and control participants

Male partners	Parameters
Sociodemographic, clinical, behavioural, lifestyle and environmental factors	Age, country of origin, length of time in Singapore if born overseas, ethnicity, education, occupation, monthly income, medical history, medication, family history, reproductive health history, male sexual function,^60^ environmental exposure, cigarette smoking, sleep,^61^ stress,^62^ dietary supplement intake, dietary and alcohol intake,^63^ chrononutrition profile,^64^ physical activity,^65^ sedentary behaviour
Anthropometric and blood pressure measures	Body height, weight, body fat composition (InBody 970, USA), blood pressure
Biochemical tests (blood/urine samples)	HbA1c, lipid profile, cortisol, oxidative stress, inflammatory biomarkers, environmental pollutants (endocrine-disrupting chemicals), exosomes, microbial-derived metabolites
Semen analysis	Semen volume, sperm density, sperm motility, sperm morphology, sperm DNA fragmentation
Molecular analysis	mRNA expressions, sncRNA expression, DNA methylation

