**Female partners**	
Sociodemographic, clinical, behavioural, lifestyle and environmental factors	Age, country of origin, length of time in Singapore if born overseas, ethnicity, education, occupation, monthly income, medical history, medication, family history, reproductive health history, female sexual function,^66^ environmental exposure, cigarette smoking, sleep,^61^ probable depression,^67^ dietary supplement intake, dietary and alcohol intake,^63^ chrononutrition profile,^64^ physical activity,^65^ sedentary behaviour
Anthropometric and blood pressure measures	Body height, weight and body fat composition (InBody 970, USA), blood pressure

HbA1c, glycated haemoglobin; sncRNA, small non-coding RNA

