### Statistical analysis plan

#### Aim 1

We will use multivariable logistic regression model to assess the association between case versus control status and male factors, adjusting for potential confounders such as male sociodemographics, general health, as well as female factors which are correlated with both male factors and successful pregnancy. We will identify these potential confounders through a literature review and conceptual framework, guided by directed acyclic graphs. We will explore propensity score methods, such as inverse probability weighting, to ensure balanced distribution of confounders across case and control groups. We will use the least absolute shrinkage and selection operator regression to select male factors for inclusion in the final model.

#### Aim 2

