We will include the identified male factors from aim 1, along with female factors which are known to be associated with successful pregnancy in a multivariable logistic regression. The male factors will focus on those easily accessible measurements. The female factors include age, BMI, smoking exposure, dietary habit, alcohol consumption and folic acid supplementation, which we have identified in our previous study.^52^ We will also include some important clinical data and other maternal factors such as the duration of active conception attempts, sexual health issues and probable depression in the logistic regression to further select the predictors. To ensure accuracy, we will use weighted logistic regression, adjusting the model based on the updated prevalence of successful pregnancies within a year in the population to correct for sampling biases. The best-fitting model will be determined using Akaike’s information criteria. Subsequently, we will create a point-based scoring system based on the final model coefficients,^53^ making it easily applicable in community settings. Integer points will be assigned depending on the presence or absence of each factor, allowing the estimation of overall probability by summing the points. Higher point values will indicate higher chances of pregnancy. To facilitate calculation of the fertility index score, all continuous variables will be categorised based on clinical thresholds or appropriate percentiles prior to the analysis. We will repeat the same procedures by including male metabolic biomarkers and semen parameters that are associated with successful pregnancy in the weighted logistic regression. This will enable the generation of various versions of the fertility index, catering to different levels of complexity for application in primary and tertiary care settings.

Subsequently, we will use 10-fold cross-validation to assess the performance of the derived logistic regression models and respective fertility index scores. This cross-validation procedure helps evaluate the model’s performance on different subsets of the data, providing an estimate of its predictive ability and generalisation performance. The fertility index will be evaluated for its discriminatory ability in predicting chances of pregnancy based on the area under the receiver operating characteristic curve (AUROC), with value >0.80 indicating that the model exhibits a good discriminatory ability or predictive value.

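### Control women report their habits while already pregnant, so several female predictors in the fertility index partly reflect behaviour changed by pregnancy

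*Protocol article*

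**What the plan says.** Under Inclusion criteria, a control couple qualifies through "female partners who are currently pregnant and with viable intrauterine pregnancy at gestational weeks of less than or equal to 16", assessed at the time of the study. Case couples are "Couples who are not able to conceive for at least 12 months of regular, unprotected intercourse".

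Under Data collection and management there is a single study visit. At it, staff gather "self-reported data on behavioural, lifestyle and environmental factor exposures from the past month using standardised questionnaires". The recall period is the one set by the validated questionnaires. Staff make the body measurements at the same visit; for the female partner, Table 1 lists "Body height, weight and body fat composition (InBody 970, USA), blood pressure". Table 1 applies alike to cases and controls. It names no pre-conception value and no pre-pregnancy weight.

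Under Statistical analysis plan, Aim 2, "The female factors include age, BMI, smoking exposure, dietary habit, alcohol consumption and folic acid supplementation". Sexual health issues and probable depression are also candidates. The coefficients become integer points, with more points meaning a higher chance of pregnancy, and an AUROC above 0.80 is read as good discrimination. Aim 1 adjusts the male associations for "female factors which are correlated with both male factors and successful pregnancy", with confounders identified from the literature and a conceptual framework, guided by directed acyclic graphs.

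**The concern.** In a case-control study a predictor should describe the time before the outcome. Here the outcome that defines a control, conception, has already happened when her habits are recorded. Many women start folic acid, stop drinking or smoking, or change their diet because they are pregnant. Sexual function and mood may change too. A case woman answering the same questions has had no such prompt.

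A difference between the groups can therefore arise from pregnancy itself, and the index would turn it into points for supposedly modifiable causes. The index is meant for people who are not yet pregnant, in community, primary and tertiary care, and for them those points would be misleading.

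The planned safeguards do not reach this. Ten-fold cross-validation, prevalence weighting, multiple imputation, propensity scores and complete-case analysis all use the same post-conception values, and the error is present in every fold. The limitations in the Discussion name recall bias, social desirability and residual confounding, but not reverse causation. The stated remedy of avoiding long recall periods keeps the window inside the pregnancy.

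**Working it through.** The plan gives no figure of its own to reproduce on this point. Its sample size does not bear on it.

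**1. Timing.** From the protocol: controls at up to 16 weeks' gestation, and a recall window of one month. Assumed: gestation counted from the last menstrual period, conception at about week 2, and a month of 30 days.
- Window length = 30/7 = 4.3 weeks.
- The whole window follows conception from week 2 + 4.3 = 6.3.
- At week 6 the share after conception is (6 − 2)/4.3 = 93%. From week 7 it is 100%.
- If pregnancy is recognised at about week 5 (assumed), the share after recognition is (9 − 5)/4.3 = 93% at week 9 and 100% from week 10 to week 16.

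**2. Size in Aim 2.** The protocol gives no behaviour rates, so every rate here is an assumption. Pre-conception habits are set equal in cases and controls, so the true odds ratios are 1 and the true AUROC is 0.50. The two items are taken as independent within each group. Patterns are ranked by likelihood ratio, and AUROC = sum over control patterns of P(control pattern) × [P(case ranks lower) + ½ P(case ties)].

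*Scenario (a).* Folic acid is 40% before conception and 90% in early pregnancy. Alcohol is 40%, and 80% of drinkers stop, leaving 8%.
- Odds ratio for folic acid = (0.90/0.10)/(0.40/0.60) = 13.5.
- Odds ratio for alcohol = (0.08/0.92)/(0.40/0.60) = 0.13.

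| Pattern | Cases | Controls | Contribution |
|---|---|---|---|
| folic acid, no alcohol | 0.24 | 0.828 | 0.828 × 0.88 = 0.7286 |
| folic acid, alcohol | 0.16 | 0.072 | 0.072 × 0.68 = 0.0490 |
| no folic acid, no alcohol | 0.36 | 0.092 | 0.092 × 0.42 = 0.0386 |
| neither favourable | 0.24 | 0.008 | 0.008 × 0.12 = 0.0010 |

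AUROC = 0.817.

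*Scenario (b), milder.* Folic acid goes from 60% to 90%. Alcohol is 20%, and 70% stop, leaving 6%.
- Odds ratios: (0.90/0.10)/(0.60/0.40) = 6.0 and (0.06/0.94)/(0.20/0.80) = 0.26.
- AUROC = 0.846 × 0.76 + 0.054 × 0.46 + 0.094 × 0.24 + 0.006 × 0.04 = 0.691.

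*Sensitivity of (a).* With the other inputs kept, pre-conception folic acid use of 60% gives 0.75 and of 80% gives 0.69. A within-group correlation of −0.2 between folic acid and alcohol lowers 0.817 to 0.796.

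*Four items* (folic acid, alcohol, smoking, diet), with favourable status before conception of 40%, 60%, 90% and 50% in both groups:
- If 30%, 30%, 30% and 20% of the remaining control women change, AUROC is 0.64.
- If 90%, 90%, 70% and 30% change, it is 0.87.

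**3. Female BMI.** An assumed gain of 1 to 3 kg at 1.60 m is 1/1.60² to 3/1.60² = 0.4 to 1.2 kg/m², in control women only. This shifts a measurement that is still mostly pre-pregnancy BMI.

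**The case against.** The strongest reply concedes the timing and disputes the reach. Most of it stands.

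- **Aim 1.** A reader might infer that the male odds ratios will be adjusted for variables caused by the outcome. The text does not fix that. It requires factors correlated with both male factors and pregnancy, chosen with directed acyclic graphs, and a correctly drawn graph excludes effects of the outcome. Bias in Aim 1 is a risk only. The graph does not repair Aim 2, and it cannot supply pre-conception values that were never collected.
- **The 0.80 criterion.** A reader might infer that the index will pass 0.80 on pregnancy effects alone. Of the two-item scenarios only (a) passes, and it needs folic acid use of just 40% among women who have tried for at least 12 months and come largely from infertility clinics.
- **BMI and age.** A reader might take every listed female factor as a consequence of pregnancy. BMI up to 16 weeks is only contaminated, and age is untouched. Nor should the female BMI shift be set against the 1.3 kg/m² planning difference, which concerns paternal BMI.
- **Men.** Their past-month items can change only through behaviour, so the problem is weaker. The male-only index is not driven directly by female habits, although the male index adjusted for the female index inherits the difficulty.
- **Forms not shown.** Medical record forms and reproductive history might hold pre-pregnancy weight. That could ease the BMI part, but not the past-month items.

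**Conclusion.** The concern holds for the female habits and symptoms in Aim 2. The control definition, the single visit, the past-month window and the predictor list are all fixed in the article. Together they place the exposure after the outcome for any control seen from about 6.3 weeks. As planned, the index coefficients and points will partly reflect behaviour changed by pregnancy.

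The direction is clear, but the size is not. Under the assumptions shown, folic acid and alcohol alone give a spurious AUROC of about 0.69 to 0.82, so the criterion of more than 0.80 could be approached or met without predictive content. The documents do not show that it will be. Female BMI is affected to a smaller degree, Aim 1 carries a preventable risk, and the men's items carry a weaker version. This should be settled while couples are still being recruited, because values not asked for at the only visit are hard to recover.

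**What to change.** Amend Data collection and management, Table 1 and Aim 2 as follows.

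- Ask control couples about the month before the last menstrual period, for the items used in Aims 1 and 2.
- Ask cases about a month while trying to conceive: the past month if they are still trying and not yet treated, otherwise the last month before treatment. An anchor at the first infertility consultation would not serve, since cases recruited through the HELMS programme may have had none and for others it may lie years back.
- Record the date folic acid was started. Use pre-pregnancy weight for control women's BMI, and do not use body fat measured in pregnancy as a predictor.
- Leave items available only from during pregnancy out of the primary index and out of the Aim 1 adjustment set.
- For couples already enrolled, re-ask these items or treat the pre-conception values as missing. Report the index with and without them.

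This needs changed questionnaire wording, a short amendment, and weights and dates from records or recall. It needs no extra couples. The downside is that control recall reaches back up to about 16 + 4.3 = 20 weeks, its accuracy may differ between cases and controls, and it departs from the questionnaires' validated past-month window. The limitations should say so.

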Therefore, in this study, we will comprehensively examine male factors of fertility, in particular, modifiable exposures, including behavioural, lifestyle and environmental factors, as well as metabolic and stress indicators. For semen parameters, in addition to basic sperm physical characteristics, we will measure sperm DNA fragmentation, DNA methylation and gene expression, as well as seminal plasma oxidative status. Information generated from these data will provide valuable insights regarding their specific relationships with male fertility and reproductive success. Importantly, the study of sperm molecular features has potential implications not only for reproductive outcomes but also for intergenerational effects, predisposing to offspring phenotypes.^20 42^ The conceptual framework of this study is presented in figure 1.

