### Participants and recruitment

Couples from the case group will be recruited from the infertility clinics in KKH, while couples from the control group will be recruited from the antenatal clinics in KKH. The team will recruit potential participants through local advertising in the hospital. We will collaborate with obstetricians and gynaecologists at KKH to obtain participant referrals. Moreover, active screening of potential participants will be conducted in the clinics. Other than from the antenatal and infertility clinics, the team will also leverage the Healthy Early Life Moments in Singapore (HELMS) programme to recruit potential cases and controls. HELMS is a new programme established at KKH in April 2022 to provide a continuum care for women with obesity in the general population before, during, and after pregnancy.^43^

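### Probable depression, sexual health issues and male stress are measured after the outcome yet can enter a forward-looking fertility index; the primary index should be built without them

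*Protocol article*

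**What the plan says.** Under Statistical analysis plan, Aim 2, the index model takes the male factors selected in Aim 1, a list of established female factors, and then "other maternal factors such as the duration of active conception attempts, sexual health issues and probable depression" for further selection. The final coefficients become integer points, and a higher total is to be read as a better chance of pregnancy. Performance is judged by AUROC, with 10-fold cross-validation and a benchmark above 0.80.

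Aim 1 regresses case or control status on male factors, with LASSO choosing among them. The section does not list those factors, but the Introduction says the study will examine "modifiable exposures, including behavioural, lifestyle and environmental factors, as well as metabolic and stress indicators", and Table 1 collects stress from male partners.

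On timing, cases are "Couples who are not able to conceive for at least 12 months of regular, unprotected intercourse". Control men have partners who are "currently pregnant and with viable intrauterine pregnancy at gestational weeks of less than or equal to 16 at the time of the study". Data collection and management begins "During the study visit (the only single timepoint visit", and behavioural, lifestyle and environmental items are "exposures from the past month using standardised questionnaires". Table 1 places female sexual function, probable depression and male stress among the data gathered there.

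**The concern.** The index is meant to tell a couple their chance of conceiving. To do that, a predictor has to describe the couple before the outcome is known. Here the outcome has already happened in both groups when mood, sexual health and stress are recorded. A failed year may plausibly change all three, and so may early pregnancy in controls. Such a change separates the groups without carrying information about a later chance of pregnancy.

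If selection retains one of these items, it receives points that a couple just starting to try would be scored on, it raises the reported AUROC towards the 0.80 benchmark, and it may displace a factor with real predictive value. The listed limitations (recall bias, residual confounding, generalisability) do not mention reverse causation. The short recall period, adopted to limit recall bias, keeps the exposure window close to a visit that follows the outcome.

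**Working it through.** **1. The plan's own figure.** Nothing in the sample size is disputed; it supplies the group sizes used below. For a BMI difference of 1.3, SD 4, two-sided 5% and 90% power, n per group = 2 × (1.960 + 1.282)² × 4² / 1.3² ≈ 199, against the stated 200. Then 200 × 1.2 = 240 per group.

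**2. Order of events.**
- Cases: attempts begin, at least 12 months pass without conception, then the visit.
- Controls: attempts begin, conception within 12 months, then the visit at up to 16 weeks of gestation.
- In both groups the outcome precedes the measurement. The article describes no measurement or recall of mood, stress or sexual function for the time before attempts began.

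**3. Whether another planned step repairs this.** Prevalence weighting corrects the sampling fractions of cases and controls. Propensity scores, stratification and interaction tests address confounding. Imputation addresses missing values. In 10-fold cross-validation every fold has the same order of events, so a reaction to the outcome would be confirmed as a predictor. None of these steps changes the timing.

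**4. Size for a binary item (assumed values, since the article gives no prevalences).** Let prevalence before attempts be q in both groups, so the true OR is 1. Let a share r of unaffected case women become affected because of the failed year, and let controls stay at q.
- p_case = q + (1 − q)r
- OR = [p_case/(1 − p_case)] / [q/(1 − q)]
- AUC = 0.5 + (p_case − q)/2
- Chance of p<0.05: two-sided comparison of two proportions, 240 per group

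| q | r | p_case | OR | AUC | chance of p<0.05 |
|---|---|---|---|---|---|
| 0.20 | 0.05 | 0.24 | 1.26 | 0.52 | 18% |
| 0.20 | 0.10 | 0.28 | 1.56 | 0.54 | 54% |
| 0.10 | 0.10 | 0.19 | 2.11 | 0.545 | 80% |
| 0.10 | 0.20 | 0.28 | 3.50 | 0.59 | >99% |

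Two further assumed contrasts, stated directly as prevalences at the visit:
- 20% vs 12%: (0.20/0.80)/(0.12/0.88) = 1.83; AUC = 0.5 + 0.08/2 = 0.54.
- 30% vs 10%: (0.30/0.70)/(0.10/0.90) = 3.86; AUC = 0.5 + 0.20/2 = 0.60.

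Across all of these the spurious OR runs from about 1.3 to 3.9 and the AUC from 0.52 to 0.60.

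**5. Size for a stress score (assumed shift).** If the failed year raises the case mean by d SD, AUC = Φ(d/√2) and the chance of p<0.05 is Φ(d√(240/2) − 1.96).
- d = 0.2: AUC 0.56, chance 59%.
- d = 0.3: AUC 0.58, chance 91%.
- d = 0.5: AUC 0.64, chance about 100%.

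**6. Limits of the illustration.** Steps 4 and 5 hold controls at the pre-attempt level. If early pregnancy also shifts them, the contrast changes: had 12% in controls become 20%, the 20% vs 12% comparison would be 20% vs 20% and the OR 1; a fall in controls would widen it. The chance of p<0.05 is a single-item guide, not the retention probability under LASSO or AIC. No multivariable AUROC gain is computed.

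**The case against.** Several points on the other side stand.

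- The items are candidates. They score points only if LASSO or AIC keeps them, and each adds little discrimination alone.
- The direction of effect is not known. The Introduction cites an association of higher stress with poorer semen quality, so part of any association may be genuine.
- The instruments are given only as citations. The past-month window is stated for behavioural, lifestyle and environmental exposures, and sexual health issues could come from the reproductive history and predate the attempts.
- The analyses already include a male-only index, which leaves out the female items, though not male stress.
- Other past-month habits share the timing. Duration of attempts, named in the same sentence, is tied to the case and control definitions and is a separate matter not relied on here.

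A reader might infer that these scales are certain to be selected, that they are purely consequences of infertility, and that they must be removed from the study altogether. The documents do not support that. Retention is possible, not certain; nothing in the article shows how much of an association would be reaction; and stress indicators are an exposure the study says it will examine, so removing them from Aim 1 would abandon a stated question. Nor does the article name male sexual function as an Aim 1 candidate: Table 1 lists it as collected, which is not the same thing.

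What these points do not answer is the order of events. With one visit after the outcome, the data cannot tell reaction from cause, and that is enough to keep the items out of a primary forward-looking score.

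**Conclusion.** The concern holds in a limited form. The plan allows states recorded after the outcome to become scored predictors of that outcome, and no planned analysis would detect or correct it. The timing follows directly from the eligibility criteria and the single visit. That male stress can reach the index is an inference from the Introduction and Table 1, since Aim 1 speaks only of male factors.

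The size rests on assumed prevalences and shifts, with no true difference before attempts and controls unchanged by pregnancy. The effect on the whole-model AUROC is unknown. The single-item effect is modest, but with 240 per group it is often large enough to reach significance. The consequence is a possible bias in the index points and its reported AUROC; the Aim 1 question itself remains legitimate if its result is described correctly.

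**What to change.** - Build the primary fertility index, and report its AUROC against 0.80, without probable depression, current sexual-function measures and male stress measures taken at the visit.
- Report a secondary index version that includes them, showing the change in AUROC and in points.
- Keep male stress indicators in Aim 1, report them as correlates of current fertility status with reverse causation named as a limitation, and do not carry them into the primary index.
- Conditions recorded as predating the attempts may remain candidates where the history records the date. Table 1 lists medical and reproductive health history only as headings, so the sponsor should confirm that onset dates are captured; if not, this option falls away.

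The cost is analysis-plan wording: no new visits, data or participants. The primary AUROC may be lower, and a genuine stress or depression effect on the chance of pregnancy would show only in the secondary version.

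### Duration of conception attempts is a candidate predictor in Aim 2 although a 12-month limit on it defines cases and controls, so an index version that keeps it would largely score the eligibility criteria

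*Protocol article*

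**What the plan says.** All places are in the protocol article.

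- Inclusion criteria, Cases: "Couples who are not able to conceive for at least 12 months of regular, unprotected intercourse".
- Inclusion criteria, Controls: "Couples with attempted time to conceive within 12 months to achieve this pregnancy". The female partner must already be pregnant.
- Statistical analysis plan, Aim 1: logistic regression is used to "assess the association between case versus control status and male factors". Aim 2 carries the selected male factors into a further logistic regression for pregnancy in the same couples.
- Aim 2 adds to the candidate variables clinical data and maternal factors "such as the duration of active conception attempts, sexual health issues and probable depression in the logistic regression to further select the predictors".
- Selection and coding: "The best-fitting model will be determined using Akaike’s information criteria", and "all continuous variables will be categorised based on clinical thresholds or appropriate percentiles prior to the analysis". Integer points are then taken from the final coefficients.
- Evaluation: "we will use 10-fold cross-validation to assess the performance of the derived logistic regression models and respective fertility index scores", judged by AUROC "with value >0.80 indicating that the model exhibits a good discriminatory ability or predictive value".
- After the main index, the plan also evaluates a male-only index, a female-only index, and the male index adjusted for the female index.

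Nothing in the article removes duration from the index, restricts how it is coded, or notes that it is also an eligibility criterion.

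**The concern.** A predictor should carry information about the outcome that was not used to assign the outcome. Here a couple becomes a case or a control partly by which side of 12 months its attempt falls on, and the length of the attempt is then offered to the model as an explanation of that status. Data collection and management describes a single study visit, and controls are already pregnant at it. A control's duration is therefore a completed time to pregnancy, not something known before the outcome.

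The second objective is an index of modifiable male and female factors, with versions for primary and tertiary care. If duration enters a version, its AUROC could clear the benchmark while saying little about those factors. The coefficient from which its points are computed may also not exist.

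**Working it through.** **1. The plan's own figures.** BMI difference 1.3, SD 4, two-sided 5%, power 90%: n per group = 2 × (1.960 + 1.282)² × 4² / 1.3² ≈ 199, or 398 in total, against the stated 400. Then 400 × 1.2 = 480, that is 240:240. The events-per-variable route also reproduces: 15 × 10 = 150; 150/0.48 = 312.5, rounded up to 313; 313 × 1.2 = 375.6, or 376. The sample size is not in dispute; the 240:240 split is used below.

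**2. Overlap by eligibility.** Cases: duration ≥ 12 months. Controls: duration ≤ 12 months. Taking both at face value, the only shared value is 12.

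**3. AUROC of duration cut at 12 months.** Let t be the share of each group at exactly 12 months. With the cut at 12 or more, all cases and a share t of controls lie above it, so AUROC = 1 − t/2. For t = 0, 5%, 10% and 20% this is 1.00, 0.975, 0.95 and 0.90. Apart from t, no distribution has to be assumed.

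**4. Percentile codings without ties.** With 240:240 the median falls on the group boundary, so median and quartile splits give 1.00. With tertiles (160 each) the middle third holds 80 of each group: 1 − ½(80/240)² = 0.944. With quintiles (96 each) the middle fifth holds 48 of each: 1 − ½(48/240)² = 0.98.

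**5. Simulation of further codings.** The article gives no duration distribution. Assumed: controls uniform over 1–11 months; cases 13 months or more with an exponential tail of mean 18 months; ties at 12 as shown.

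| Coding of duration | No ties | 20% of each group at 12 |
|---|---|---|
| Continuous (for reference) | 1.00 | 0.98 |
| Cut at 12 months | 1.00 | 0.90 |
| Median | 1.00 | 0.90 |
| Tertiles | 0.95 | 0.95 |
| Quartiles | 1.00 | 0.95 |
| Quintiles | 0.98 | 0.98 |
| Single cut at 6 months | 0.73 | 0.68 |
| Single cut at 24 months | 0.78 | 0.72 |

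**6. Comparison with a genuine predictor.** The one effect size in the article, BMI, gives AUROC = Φ(1.3 / (4√2)) = Φ(0.230) = 0.59. In simulated 10-fold cross-validation (with a light ridge penalty, because the unpenalised estimate diverges) BMI alone gave 0.58. Adding duration cut at 12 months gave 1.00.

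**7. Would AIC keep it?** Unweighted, the constant-only deviance is 2 × 480 × ln 2 = 665.4, so AIC = 667.4. With duration cut at 12 and no ties the deviance tends to 0 and AIC to 4. With 20% ties, the group at 12 or more holds 240 cases and 48 controls: deviance = −2[240 ln(240/288) + 48 ln(48/288)] = 259.5, AIC = 263.5. Retention is to be expected in both situations.

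**8. Finite coefficient?** Below any cut at or under 12 months there are no cases; above any cut at or over 12 there are no controls. One cell of the two-by-two table is empty, so separation is complete, or quasi-complete with ties, and the maximum-likelihood log odds ratio is not finite.

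**9. Do the planned safeguards help?** Cross-validation does not: every fold is drawn from couples selected by the same rule. Prevalence weighting does not: one weight per group leaves the within-group distributions, and so the AUROC of duration alone, unchanged.

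**The case against.** Several points against the concern stand and limit it.

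- Duration is one example in a list of candidates, not a fixed component of the index. Its inclusion is expected under AIC but not certain.
- Continuous variables are categorised before the analysis and no cut is named for duration. A continuous term is therefore not the planned index analysis, and cuts far from 12 months can leave duration alone below 0.80.
- The case criterion speaks of regular unprotected intercourse, the predictor of active attempts. A couple could meet the first while reporting a shorter period of the second, so a case value below 12 months is possible on the text. Misreporting would have the same effect.
- A non-finite coefficient and an inflated AUROC are different failures. With an empty cell, points cannot be derived and the problem should surface during model building. With penalisation, or a few discordant reports filling the cell, the model fits and the inflated AUROC is what remains.

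A reader might go further and infer that the AUROC is 1.00 by definition, that every version containing duration must pass 0.80, or that Aim 2 cannot be answered. The article does not support this. The first two depend on the coding, on ties and on how duration is recorded. The third overlooks the separate male-only evaluation: duration is listed with clinical and maternal variables, so that index is not directly affected.

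Two defences do not stand. Duration can be a legitimate predictor in a prospective cohort, but not where it was used to assign the groups. Nor is this a detail left out of a condensed article: entering duration is a stated choice.

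**Conclusion.** The concern holds in limited form. A variable that all but restates the 12-month eligibility rule is a candidate predictor of case or control status, and AIC, weighting and cross-validation cannot correct for that. In a version that retains it, the AUROC largely reflects eligibility: about 1.00 for duration alone at a 12-month or median cut, 0.90 with 20% ties, and 0.90 or more for every percentile coding tried, against 0.80. Single cuts at 6 and 24 months give about 0.73 and 0.78.

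The 12-month figures rest on the eligibility limits, an assumed share of ties, and recorded duration agreeing with those limits. The 6- and 24-month figures also rest on assumed distributions. The lack of a finite coefficient holds as long as no discordant reports fill the empty cell.

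Affected are all index versions containing duration and, if duration is placed in the female index, that index and the male index adjusted for it. This should be corrected before the models are fitted.

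**What to change.** In the Statistical analysis plan, Aim 2, delete duration of conception attempts from the candidate predictors of all index versions, including the female index. Add one sentence stating that variables which define case or control eligibility are not eligible as predictors. Keep duration only to describe the two groups.

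The cost is a small text change. Data collection, recruitment and the sample size of 480 couples are unchanged. The AUROC of the resulting index can be expected to be lower, but it will then reflect the male and female factors that Aim 2 is about.
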